## Abstract

**Background:**

The aging trend of people living with HIV or AIDS in China is increasing day by day. Frailty is a common condition among older adults living with HIV or AIDS and represents a significant cause of poor prognosis, including falls, decreased quality of life, increased mortality, and potentially prolonged hospital stays. Consequently, early frailty screening in this population holds important clinical significance.

**Objective:**

This study aims to describe the theoretical basis, research objectives, and implementation plan of a prospective observational study. It will focus on investigating the current status of frailty syndrome in hospitalized older adults living with HIV or AIDS, while simultaneously exploring the development of a clinically applicable risk prediction model.

**Methods:**

This study is an ongoing single-center prospective observational study, with a plan to recruit at least 556 hospitalized older adults living with HIV or AIDS (n=445 for development and n=111 for validation). According to the theory of unpleasant symptoms, candidate predictors are categorized into physiological factors (including sociodemographic factors, disease-related influencing factors, sleep, nutrition, and neurocognitive function), psychological factors (including anxiety and depression status), and environmental factors (including social support status). Potential predictors are screened using univariate analysis and least absolute shrinkage and selection operator regression to identify variables for final model inclusion. Model construction and validation employ 3 standard machine learning algorithms: logistic regression, random forest, and support vector machine. Model performance will be evaluated by reporting accuracy, precision, sensitivity, specificity, and the area under the curve.

**Results:**

This study is conducted at a designated infectious disease hospital in Changsha, Hunan Province, China. Participant recruitment commenced on December 22, 2024, and as of December 5, 2025, a total of 603 patients have been enrolled. The primary study findings are anticipated to be published in August 2026.

**Conclusions:**

The findings of this study are expected to provide clinicians in the department of infectious diseases with a convenient tool for frailty risk prediction, thereby enabling early intervention and ultimately improving the long-term health status and quality of life of people living with HIV.

## Introduction

With the promotion and application of highly active antiretroviral therapy, the treatment prospect of AIDS has been significantly improved. Highly active antiretroviral therapy effectively suppresses viral load, controls disease progression in people living with HIV, prolongs survival, and enhances quality of life. The increased survival rate has led to a growing population of people living with HIV or AIDS aged ≥50 years [1]. Consequently, the Centers for Disease Control and Prevention in the United States defines individuals aged ≥50 years with HIV as the “older adult population” rather than the commonly defined population aged ≥60 years [2]. Older adults living with HIV or AIDS face not only age-related disease risks but also chronic HIV-associated conditions and synergistic interactions between HIV and non-HIV comorbidities [2]. Chronic immune damage and inflammation contribute to declining physical function and resilience, predisposing them to frailty—a dynamic geriatric syndrome. The weakened state can lead to a higher risk of adverse events for people living with HIV or AIDS, which is an independent risk factor for new chronic diseases, falls, cognitive decline, multidrug treatment, hospitalization, loss of independence, and increased mortality [3]. Thus, early identification of frailty and implementation of targeted preventive measures are critically important.

Frailty represents a complex state. Strain’s study analyzed neuroimaging markers (including diffusion tensor imaging and cerebral blood flow), revealing that frailty in people living with HIV or AIDS correlates with structural and functional brain alterations, specifically impaired psychomotor speed and executive function performance [4]. HIV-infected individuals who are in a frailty state exhibit atrophy in the anterior cingulate cortex and cingulate cortex regions, which is associated with a decrease in their quality of life. A multidimensional study of HIV-infected adults at the University of California also confirmed this result, showing that frailty has a significant negative impact on the health-related quality of life of people living with HIV or AIDS, and the impact on people living with HIV or AIDS is significantly stronger than that on uninfected adults [5]. In addition, statistical analysis of clinical events following baseline frailty assessment elevated cardiovascular disease risk in frail older adults living with HIV or AIDS (incidence rate ratio of 3.83), followed by new-onset diabetes and orthopedic disorders [6].

The impact of frailty on cognitive function in older adults living with HIV or AIDS is increasingly recognized. HIV-associated neurocognitive disorders (HAND) are one of the most common complications of HIV-related nervous system diseases. According to the diagnostic criteria of the US HIV Neurobehavioral Research Center in 2007, HAND can be divided into asymptomatic neurocognitive impairment, HIV-related mild neurocognitive disorder, and HIV-related dementia [7]. Research has shown that the incidence of HAND in people living with HIV or AIDS over 50 years old is as high as 40.5% to 54.8% [8,9], and there is a synergistic effect between cognitive impairment and frailty [10], that is, frailty can lead to a decline in cognitive function and a higher risk of cognitive impairment. Conversely, impaired cognitive function can also exacerbate the process of frailty. Through a 1-year follow-up study of 60 people living with HIV or AIDS, half of the participants experienced varying degrees of cognitive impairment after the follow-up, with higher levels of frailty indicating a greater risk of cognitive impairment [11]. Notably, both prefrailty and frailty status significantly correlate with HAND, especially mild neurocognitive disorder, further confirming that frailty is an important cause of HAND occurrence [12].

Currently, unidimensional frailty assessment remains predominant in research involving people living with HIV or AIDS, while research on multidimensional frailty status is still insufficient, and the factors leading to multidimensional frailty in hospitalized older adults living with HIV or AIDS are not yet clear. Therefore, we will explore multidimensional frailty as the main outcome. The theory of unpleasant symptoms (TOUS), as a mid-level theory, is commonly used to establish methodological methods and analyze results, or as a theoretical framework for analyzing influencing factors [13,14]. The theory suggests that factors that affect symptoms can be divided into 3 parts: physiological, psychological, and environmental. The three interact and influence each other, jointly affecting disease symptoms and influencing the outcome of symptoms. Guided by TOUS, we categorized potential frailty factors in hospitalized older adults living with HIV or AIDS into physiological, psychological, and environmental domains based on literature review and clinical practice. Ultimately, all included potential influencing factors were identified and finalized through online expert consultation.

Early-stage frailty in older adults living with HIV or AIDS is often relatively insidious. However, to our knowledge, there is relatively little research and development in China on frailty prediction tools for hospitalized population. To address these gaps, we aim to develop and validate a prediction model using 3 machine learning algorithms. By comparing their performance, we seek to enhance risk prediction accuracy, ultimately improving patient prognosis and health outcomes.

This prospective observational study aims to (1) determine the prevalence of multidimensional frailty among hospitalized people living with HIV or AIDS aged ≥50 years, (2) identify factors associated with frailty guided by the TOUS, and (3) develop and validate risk prediction models.

## Methods

### Ethical Considerations

This prospective observational study protocol has been approved by the Medical Ethics Office of Changsha First Hospital (approval number: Ethics Committee: [2025] Express Review [Clinical Documents] No.12) and the Medical Ethics Committee of University of South China (approval number: 2024HLSC025) and registered on ClinicalTrials.gov (ChiCTR2500103387) to ensure transparency and compliance with best practices.

Written informed consent from all participants is required before participating in the study. During the research, all personal data collected (such as identity information, date of birth, medical payment, health information, etc) will be encoded and replaced to protect the identity of participants and be protected under applicable laws. Only researchers and authorized personnel can access these materials. The research results will be reported and disseminated through open and transparent peer-reviewed journals and conference reports.

This study is a noncommercial academic research study and does not provide any direct financial compensation to the participants. All participants receive professional personalized health guidance and counseling based on their examination results, which is the main benefit of their participation in this study.

### Participants and Qualifications

The inclusion and exclusion criteria are presented in Textbox 1.

Textbox 1.Inclusion and exclusion criteria for a prospective observational study.
**Inclusion Criteria**
People living with HIV or AIDS, who are diagnosed according to the HIV/AIDS virus infection diagnosis industry standard (WS 293-2019) [15]Age ≥50 yearsClear awareness and ability to cooperate in completing investigations and testingVoluntary participation and provision of informed consent
**Exclusion Criteria**
Physical functional impairments such as severe language communication barriers, hearing impairments, or visual impairments that hinder normal assessmentHemiplegiaRefusal to sign the informed consent form

### Patient Recruitment

All eligible patients will be recruited within 24 to 48 hours after admission. Trained researchers will determine potential participants based on inclusion and exclusion criteria and explain this observational study to patients and their families. After patients confirm and sign informed consent forms, they will be included in this study. The examination results and related data of all participants will be subject to strict confidentiality management to ensure the privacy and security of patients. Participants have the right to withdraw from the study in any form at any stage. We plan to recruit at least 556 hospitalized older adults living with HIV or AIDS (n=445 for development and n=111 for validation). The research evaluation will be completed during the patient’s hospitalization period.

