### Sample Size

Frailty occurrence in people living with HIV or AIDS represents a binary outcome. Previous studies reported a frailty incidence of 59.3% in hospitalized older adults living with HIV or AIDS, which was assessed using the FRIDE frailty scale [16]. Due to the current lack of a frailty prediction model for HIV/AIDS patients, it is not possible to determine *R*^2^ through previous models. Based on the proportion of outcome events, the maximum *R*^2^ (*R*^2^ cs_max) is calculated to be 0.7416. Assuming that the new model can explain 20% of the variability, the expected *R*^2^ is 0.1483 (=0.7416×20%). We expect the predictive model to include 5 to 10 predictor variables, based on “pmsampsize(type=‘b’, csrsquared=0.1483, parameters=10 , prevalence=0.593).” In this formula, csrsquared represents the ability of the expected prediction model to explain outcome variability; parameters represent the total number of candidate variables expected to be included; and prevalence refers to the prevalence of frailty events in older people living with HIV or AIDS in China based on previous research. The calculation indicates that a minimum sample size of 556 is required. A total of 330 events were expected, corresponding to 33 events per predictor variable. The above results are calculated using the pmsampsize package in R Statistical Software (version 4.4.0) [17].

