### Model Development and Validation

The sample size of this study is relatively small. This study uses logistic regression (LR) as the benchmark for performance comparison. LR has certain advantages in handling limited sample sizes and can demonstrate feature coefficients and significance levels. Although random forest (RF) has the risk of overfitting in small sample situations, it has certain advantages in handling complex nonlinear relationships. We will minimize the risk by adjusting decision tree parameters and cross-validation. Support vector machine (SVM) is particularly suitable for handling situations with high feature dimensions but relatively small sample sizes, and its regularization properties help control the risk of overfitting. As one of the tree ensemble algorithms, XGBoost also has the risk of overfitting and relatively complex parameter tuning. Neural networks have high requirements for sample size and poor clinical interpretability for small sample studies. We hope to ensure the robustness of the model to a large extent in this small sample study. For future larger-scale research, more complex machine learning methods will be used.

Randomly split the training set and validation set in a 7:3 ratio, and use the following machine learning algorithms for modeling: LR model, RF, and SVM. Univariate analysis combined with least absolute shrinkage and selection operator regression will be used to screen predictive factors. To address nonlinearity, we will analyze the relationships between relevant factors and HIV frailty risk using restricted cubic splines and incorporate them as spline terms in the model. Restricted cubic splines can also indirectly capture potential interactions between features. Interactions and complex nonlinear decision boundaries will be handled by selecting nonlinear kernel functions in SVM. The primary model performance evaluation metric is accuracy, which represents the proportion of correctly predicted samples in classification tasks. This will be considered alongside precision, recall, *F*_1_-score, and area under the receiver operating characteristic curve for comprehensive assessment. Through integrated comparison, the algorithm achieving optimal balance across these metrics will be selected as the final model for predicting frailty status in people with HIV.

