To prevent overfitting, the nonlinear modeling effects of all models will be validated via cross-validation. A 3×10-fold cross-validation scheme will be adopted, with each split performed independently, yielding 30 model performance estimates (eg, area under the curve [AUC], *F*_1_-score). Overfitting will be monitored by ensuring that the performance difference between the training set and the cross-validation set remains below a threshold (AUC difference <0.05). During cross-validation, hyperparameters (including max_depth for RF, and C and γ for SVM) will be jointly optimized to select the parameter combination that achieves the best trade-off between fitting efficacy and generalization ability, thereby further reducing overfitting risk. The final model selected through cross-validation will then be evaluated on an independent test set for ultimate performance assessment. For internal validation, we performed bootstrap resampling (n=1000 iterations) to generate training sets matching the original cohort size. Retraining prediction models with these training sets and evaluating performance using the above indicators, we will repeat this process to obtain internal validation performance. External validation will be implemented in prospective observational studies, using external period validation to analyze samples from September 1, 2025 to December 31, 2025. In future research, we plan to collaborate with other institutions to continue external validation. The sample size required for external validation in this study is 1/4 of the modeling sample size, and the minimum sample size for external validation is calculated to be 139 cases (Figure 1).

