## Results

This study is conducted at a designated infectious disease hospital, the First Hospital (Infectious Diseases Hospital) of Changsha City, Hunan Province, China, which is one of the professional designated treatment centers for HIV/AIDS in China. It is supported by the Traditional Chinese Medicine Research Program of the Health Commission of Changsha, Hunan Province (no. B202318) and the Hunan Provincial Natural Science Foundation of China (no. 2023JJ60388). The study was planned to be conducted from December 2024 to August 31, 2025, with external validation conducted from September 1, 2025, to December 31, 2025. Recruitment for the study began on December 22, 2024. As of December 5, 2025, a total of 603 patients have been recruited. Currently, no data analysis has been conducted. The primary study results are expected to be announced in August 2026.

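### The 556 needed to develop the model is also used as the recruitment total and divided; the 445/111, 7:3 and 139 figures cannot all hold, and either split leaves training below 556

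*Protocol article*

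**What the plan says.** All statements are in the protocol article.

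- **Sample Size.** The calculation is run with "csrsquared=0.1483, parameters=10 , prevalence=0.593" and concludes: "The calculation indicates that a minimum sample size of 556 is required". It is expressed as 330 events, or 33 per predictor.
- **Patient Recruitment**, and likewise the Abstract: "We plan to recruit at least 556 hospitalized older adults living with HIV or AIDS (n=445 for development and n=111 for validation".
- **Model Development and Validation**, on building the models: "Randomly split the training set and validation set in a 7:3 ratio". The sample to be divided is not named.
- **Model Development and Validation**, on external validation: the external set is to be a quarter as large as the set used for modelling, with this result: "the minimum sample size for external validation is calculated to be 139 cases". The external sample consists of patients from 1 September to 31 December 2025. The section also plans 3×10-fold cross-validation, 1000 bootstrap resamples, and a final evaluation on an independent test set. It does not say whether that test set is the 30%, the 111 or the 139.
- **Results.** The main study was planned to run to 31 August 2025, with external validation after that. "As of December 5, 2025, a total of 603 patients have been recruited", and no data had yet been analysed.

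**The concern.** A sample size computed with these inputs is a requirement for the data on which the model is fitted. The plan uses 556 in that sense when it derives the number and again when it takes a quarter of it for external validation. In the Abstract and Patient Recruitment, 556 is instead the number recruited, and development receives only part of it. The 7:3 split then removes a further 30% from a sample that is not named.

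Two things are at stake. First, the fitted model may rest on far fewer patients than the plan says it needs, with more overfitting than the sizing allows for. Second, a reader of the eventual report could not tell which of 445, 389, 311 or 556 was the planned training set, or which sample is the independent test set on which the final model is judged.

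**Working it through.** **Inputs from the plan.** Cox-Snell R² 0.1483, P = 10 parameters, prevalence 0.593; 556; 445/111; 7:3; one quarter and 139; 603 enrolled from 22 December 2024 to 5 December 2025.

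**Assumption.** Target shrinkage S = 0.90, the package default. The stated call sets no other value.

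**1. Reproduce 556.** The shrinkage criterion is n = P / [(S − 1) ln(1 − R²/S)]. Here ln(1 − 0.1483/0.90) = −0.18006, so n = 10 / (0.1 × 0.18006) = 555.4, rounded up to 556. The other criteria give smaller numbers: 244 for optimism in R² and 371 for the overall risk within ±0.05. Events: 556 × 0.593 = 330, or 33 per parameter. The stated figure is right. (The maximum R² computes to 0.7411 where the plan has 0.7416; this does not change n.)

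**2. What each statement implies.**

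- 445/111: 556 × 0.8 = 445 and 556 × 0.2 = 111. Also 445/4 = 111.
- 139: 556/4 = 139, so the modelling sample is 556 and the total is 556 + 139 = 695.
- 7:3 of 556: 389/167. 7:3 of 445: about 311/134. 7:3 of all 603: 422 in training. 7:3 of 695: about 486 in training.

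The quarter rule gives 111 if development is 445, and 139 if it is 556. The two results belong to different development samples.

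**3. Can they be reconciled?** A 7:3 split nested in a 556 modelling sample, with 139 later patients added, is coherent. Training is then 389, 445/111 has no place, and the recruitment minimum should read 695. Taking 445/111 as correct makes 139 wrong. For training to hold 556 after a 7:3 split, 556/0.7 = 794.3, so 795 patients would be needed before any external sample.

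**4. Size of the shortfall.** Solving the formula in step 1 for S at each n with P = 10, and for P at S = 0.90 (P = n × 0.018006):

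| Training n | Expected shrinkage | Parameters at 0.90 |
|---|---|---|
| 556 | 0.900 | 10.0 |
| 445 | 0.878 | 8.0 |
| 437 | 0.877 | 7.9 |
| 422 | 0.873 | 7.6 |
| 389 | 0.864 | 7.0 |
| 311 | 0.835 | 5.6 |

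These values are for an unpenalised regression.

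**5. Accrual.** 603 in 349 days is 1.728 per day. The split of the 603 around 1 September is not reported. If accrual was constant (assumption):

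- through 31 August: 253 × 1.728 ≈ 437, or about 306 in training after 7:3;
- September to December: 122 × 1.728 ≈ 211;
- total by 31 December: about 648.

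Reaching 695 would need (695 − 603)/26 ≈ 3.5 per day.

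**6. Precision in validation.** Hanley-McNeil 95% half-width at prevalence 0.593. The plan gives no AUC, so a range of 0.70 to 0.85 is assumed. From AUC 0.70 to 0.85 the half-width runs from 0.10 to 0.07 at n = 111, from 0.09 to 0.06 at n = 139, and from 0.07 to 0.05 at n = 211.

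**The case against.** The strongest reply is that these are layers, not rival partitions: a random 7:3 split within the modelling sample supplies the test set, and a later-period sample supplies external validation. That is a fair reading, and it is why the statements conflict jointly and not pair by pair. It still leaves 445/111 unexplained and training at 389.

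A second reply is that 556 is a floor and enrolment had already passed it. If all 556 are used for modelling, development does meet its requirement and only the stated total is short. A reader might infer that the study will therefore end below 695. At the observed rate that is likely, but recruitment was open until 31 December and the documents do not prove it.

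A reader might also infer that membership of every set can be chosen after results are seen. The documents do not support that: external validation is fixed by calendar date, the 7:3 split is random, and no analysis had been done. What is open is which sample the split divides.

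Three limits also stand. The shrinkage figures describe unpenalised regression, while the plan uses LASSO screening, random forest and support vector machine as well. The fall to 0.878 at 445 is modest. A random hold-out beside cross-validation, bootstrap and temporal validation is inefficient, but it is not in itself an error. The flow chart is not visible in the text available; whatever it shows, the written numbers disagree.

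**Conclusion.** The point holds. The 556 is correctly computed as a development requirement, then reused as the recruitment total and divided. No single reading satisfies 556, 445/111, 7:3 and 139 together. Under any reading that applies the 445 or the 7:3 split, training falls short of 556, with expected shrinkage between about 0.878 and 0.835 against an assumed target of 0.90. If all 556 are modelled, the deficit is 139 in the stated total.

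The contradiction needs no assumption. Its size rests on the 0.90 default, on 10 parameters, and on regression without penalty. The counts by date rest on constant accrual. Because no analysis has been done, it can still be settled without bias, and it should be settled before analysis begins.

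**What to change.** Before any analysis, state one partition and use it consistently in the Abstract, Patient Recruitment, and Model Development and Validation.

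- Keep the dates already fixed. Development is everyone enrolled through 31 August 2025. Temporal validation is everyone enrolled from 1 September to 31 December 2025, not capped at 111 or 139.
- Fit on the whole development set. Use the planned cross-validation and bootstrap, with optimism correction, in place of the random 7:3 hold-out.
- Replace 445/111 and 139 with the actual counts, and say which set is the independent test set.
- State what those counts support. This partition does not by itself restore 556. With about 437 in development (constant accrual assumed), expected shrinkage is about 0.877 for 10 parameters, or 7.9 parameters at 0.90. Give the expected AUC precision in the validation set; at about 211 patients it is ±0.05 to ±0.07 for an AUC of 0.70 to 0.85.

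If the sponsor prefers to keep the 7:3 split, name the sample it applies to and do not claim that 556 is met for development.

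The cost is protocol wording and the loss of the random hold-out estimate, which resampling and the later-period set replace. No extra patients are needed.
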